Appendix H: INFORMATION SHEET FOR PLAYERS' PARENTS OR LEGAL GUARDIANS

Appendix I: INFORMED CONSENT FORM

Appendix J: DATA ANALYSIS TABLE

Appendix K: QUESTIONNAIRE FOR COACHES

Appendix L: 11+ WARM UP EXERCISES

Appendix M: CONTENT FOR THE TRAINING

Appendix N: THE "11+" RECORDING FORM

## GLOSSARY OF TERMS

**Coach:** One who instructs players in the fundamentals of a competitive sport and directs team strategy (Merriam-Webster Online Dictionary, 2010).

**Exposure factor:** Individual participation time recorded (Hägglund, Waldén, & Ekstrand, 2006)

**Recurrent injury:** injury of the same type and at the same site which occurs after a player's return to full participation within two months (Fuller et al., 2006).

**Injury prevention:** the implementation of interventions to eliminate or reduce the likelihood and the severity of injuries caused by external or internal mechanisms before they occur (Lawrence, 2008).

**Injury severity:** Based on absence from game or practice participation: slight (1–3 days), minor (4–7 days), moderate (8–28 days), major (>28 days) (Fuller et al., 2006).

**Rehabilitation:** A player is considered injured until given clearance by medical staff to participate fully in team training and match play (Hägglund et al., 2006).

**Soccer Injury:** Any physical complaint resulted for soccer participation whether in training or match (Junge & Dvorac, 2000).

**Training session:** Coach directed physical activities (on field, gym, recovery sessions, aerobics) carried out with the team (Hägglund et al., 2006).

**Readiness for injury prevention:** Coach related factor that is assumed to influence sports injury outcomes (Siwon, 2013).

## **CHAPTER 1: INTRODUCTION**

### **1.1 BACKGROUND OF THE STUDY**

The practice of soccer predisposes players to encounter an increased number of injuries over time due to the high intensity nature of the game and contacts (Alentorn-Geli et al., 2014). Many studies have indicated that the lower extremities are the parts of the body that are most frequently affected by injuries. Some have shown that the ankle joint was the most affected part (Luciano & Lara, 2012), others the knee joint (Alentorn-Geli et al., 2014) and others the thigh (Ekstrand, Hägglund, & Waldén, 2011).

Since soccer is a contact game, many injuries are considered to be of traumatic nature where ankle and knee sprains were observed to be the most encountered injuries (Nilstad, Andersen, Bahr, Holme, & Steffen, 2014). A recent study conducted in Brazil indicated that most injuries were muscular and most occurred as the result of collisions with other athletes (de Freitas Guina Fachina et al., 2013). In other studies, the lower back, Achilles tendon, groin, patellar tendon, and lower leg are the typical sites of overuse injury observed among soccer players (Kristenson et al., 2013).

Junge and Dvorak (2004) concluded that the nature and severity of injuries hamper the performance of players and that every soccer player participating in high level competition sustains at least one injury that will hinder the performance. There is significant medical and economic cost associated with sports injury affecting athletes, teams and society. Sports injuries were estimated directly to cost the Australian community at least \$1.65 billion 1998 (Orchard & Finch, 2002). Looking at the situation in Rwanda where players and teams have economic difficulties, soccer players might have trouble managing their injuries. However, few reports have been done to ascertain the burden of soccer injuries in terms of cost.

Suggestions have been made to counter the occurrence of injuries. In accordance with the framework developed by Van Mechelen, Hlobil, and Kemper, (1992) and later upgraded by Finch (Finch, 2006) preventive measures should be based on epidemiological research. The first two steps in injury prevention in a given sporting activity should be the establishment of the extent, incidence, severity and profile of injury. In Rwanda, a few systematic epidemiological studies looking at soccer-related injuries were conducted that focus on the type, severity, and management of injuries, the need for physiotherapy intervention (Twizere, 2004) among male

players, and factors associated with sports injuries among female soccer players (Niyonsenga & Phillips, 2013). Although these studies used different methods of data collection and the definition of injury, they highlighted that the number of injuries were high and recommended injury prevention intervention.

From a public health perspective, prevention of injuries should consider all the factors that constitute a chain of events leading to injuries. Therefore injury prevention programmes should be designed to help players avoid incidents ('pre-event' measures), to avoid immediate severity of injury in case an incident happens ('event' measures), or to minimise the consequences of a sustained injury ('post-event' measures) (Henke & Luig, 2012). These steps could be further summarized as primary, secondary or tertiary levels of injury prevention. Henke and Luig, (2012) summarized injury prevention measures using the Haddon-injury prevention matrix (Figure 1) following the comprehensive injury causation model developed by Bahr and Krosshaug (2005) indicating all the intrinsic and extrinsic factors predisposing players to injuries.

Figure 1: Haddon Intervention Matrix with Examples of Sport Injury Prevention Measures

(Henke & Luig, 2012)

|                     |                                     | FACTORS                                                                   |                                                     |                                                                             |
|---------------------|-------------------------------------|---------------------------------------------------------------------------|-----------------------------------------------------|-----------------------------------------------------------------------------|
| Phase               |                                     | Human                                                                     | Equipment                                           | Environment                                                                 |
| Pre-Accident        | Accident prevention                 | Risk awareness
Pre-season conditioning
Strength training
Warm-up | Braces
Proper foot-ware
Playing field surface | Fair play rules
Playing field management
Safety rules and regulations |
| Injury-event        | Injury-prevention                   | Fall techniques
Impact coping techniques                               | Skin guards
Mouth protection
Face guards      | Padded goal posts
Shock absorbing surfaces                               |
| Post-accident Event | Injury treatment and rehabilitation | Fair training
Compliance to "return-to-play" rules                     | First aid equipment
Emergency equipment          | Emergency and rescue services
Medical care and rehabilitation services   |

Many studies that have been conducted in soccer assessing the effectiveness of injury prevention focused mainly on the primary (Junge et al., 2011) and tertiary injury prevention strategies. However, there are few studies that focused on the secondary injury prevention. Therefore there is a need for more studies to investigate the effectiveness of strategies targeting all the levels to prevent injuries in soccer. For example, a study conducted by Mandelbaum et al.(2005) assessed the benefits of performing neuromuscular and proprioceptive exercises on the reduction of knee injuries with emphasis to the Anterior Cruciate ligament. Another study tested the effect of a stretching technique on the occurrence of hamstring strain among elite soccer players (Arnason, Andersen, Holme, Engebretsen, & Bahr, 2008). Many other research attempts were conducted looking at the effectiveness of other techniques in injury prevention. Even though studies vary in many areas such as the population, the designs, and the intervention used, they conclude that soccer injuries can be prevented and suggest that multi-component intervention studies would be effective.

Following proposed multiple factor intervention strategies, recent studies were conducted using the model developed by the F-MARC. The F-MARC developed an injury prevention programme called the “11+” composed of structured exercises performed during warm up plus the promotion of fair play. The results of studies conducted using the “11+” programme show the reduction in the risk of injuries (RR 0.65; 95% CI 0.46 to 0.91) (Soligard et al., 2010), severe (RR 0.47; 95% CI 0.26to0.85) as well as overuse injuries (RR 0.55; 95% CI 0.36 to 0.83) (Soligard et al., 2008). Additionally, other studies highlighted that the programme increased proprioception, static and dynamic balance (Daneshjoo, Mokhtar, Rahnema, & Yusof, 2013), functional balance (Kathrin Steffen et al., 2013) and concentric hamstring strength (Daneshjoo et al., 2013). However, the results of other studies do not indicate significant effect of the “11+” programme (van Beijsterveldt et al., 2012; Steffen, Myklebust, Olsen, Holme, & Bahr, 2008). The major limitation for these studies was lack of coaches and players’ compliance in the implementation of the programme. Therefore there is a need to further investigate the evidence on the effectiveness of the “11+” programme on the prevention of injuries in soccer.

Studies that investigated the second level of injury prevention are scarce. Correspondingly the F-MARC developed the guideline that could be used by soccer people to decide if the player could continue playing in case of injury. However, many injuries could be aggravated when the players

are allowed to resume training or competition without any sort of care or appropriate assessment. Therefore there is a need for an interventional study that focuses on the outcome of implementation of first aid and return to activities in teams that do not have any medical personnel.

According to Hägglund, Waldén and Ekstrand, (2007) players in the teams without any medical personnel have difficulties to get appropriate treatment and rehabilitation of their injuries. The authors conducted a study involving coaches on return to play decision of injured players among teams that did not have any medical personnel. The results indicate that the rate of sustaining a re-injury was lower among the teams after the intervention. Moreover, there is a need to assess the incidence of the re-injuries among team that have and teams that do not have medical personnel.

The role of the coach is valuable in maintaining health, safety and success of the players (Sharkey & Gaskill, 2006). While supervising players during training and competition, the coach should recognize potentially risky situations and develop strategies to minimize them. On the contrary, often coaches are not equipped with the necessary knowledge for them to identify the risk of injuries, treatment, rehabilitation and the modalities for prevention (Andersen, Courson, Kleiner, & McLoda, 2002). However, little is known about what coaches know regarding injury prevention. It would be of great importance to assess the level of knowledge of the coaches in first aid and injury prevention. Furthermore, they should be trained in emergency and first aid to improve their knowledge.

## **1.2 STATEMENT OF THE PROBLEM**

In Rwanda a large number of young people participate in soccer at different levels. Players incur injuries as they increase their involvement in trainings and matches. As mentioned by Junge and Dvorak (2004) players sustain performance limiting injuries every year. Players in Rwanda may have serious problems with their performance that may be due to the severity of injuries and extended period of time without playing. Therefore many players may not have the opportunity to proceed to high performance and top level play. The development of the young players may also be affected as a result of injury where psychological and behavioural problems were displayed (Verhagen, van Stralen, & van Mechelen, 2010).

Injury prevention has been advocated to help players to stay injury-free by proper training, warm up, cool down, stretching and adequate recovery (Kirkendall, Junge, & Dvorak, 2010; Colin Fuller, Junge, & Dvorak, 2012). Additionally a study conducted in Rwanda shows the need for preventive measures as soccer players are threatened by the reduction of their performance and stop their careers at an early stage due to injuries (Twizere, 2004). Coaches and players should be aware and take the lead to minimize the risk for injuries and follow appropriate treatment and rehabilitation principles. However, coaches and players may have deficits in the knowledge and implementation of injury prevention measures. Moreover, teams may be experiencing insufficient financial resources and shortage of medical personnel. There is a need for injury prevention intervention programmes targeting coaches to address injuries in youth soccer in Rwanda.

### **1.3 AIMS AND OBJECTIVES OF THE STUDY**

#### **Study one**

##### **AIM**

The purpose of the study is to establish an injury surveillance system in soccer teams in Rwanda.

##### **Objectives**

- a. To determine the difference in etiology, nature, severity and location of injuries between first and second division soccer players
- b. To assess whether there is any relationship between injury pattern and players' age, playing position and division of play.
- c. To determine whether nonmodifiable and modifiable intrinsic risk factors predict the risk of sustaining an injury in male soccer players in Rwanda.
- d. To assess if there is any difference in injury pattern according to training and match exposure
- e. To determine whether the availability of the medical support into the teams is associated with the incidence of re-injuries

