### **2.3.2 Objectives**

- a. To determine the difference in etiology, nature, severity and location of injuries between first and second division soccer players
- b. To assess whether there is any relationship between injury pattern and players' age, playing position and division of play.
- c. To assess if there is any difference in injury pattern according to training and match exposure
- d. To describe the availability of the medical support into the teams

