### **2.3.6 Procedure**

#### **2.3.6.1 Data collection**

Ethical approval for the study will be sought from the University of Cape Town. Permission to conduct the study will be requested from the ministry of sports and culture, and FERWAFA. Finally, permission will be sought from the teams in the first and second division. Written consent will be obtained from the coaches and players from both divisions as well as for the parents or legal guardians of under 18 players (Appendices F, G, H, I).

Physiotherapists with Bachelor's degree will be recruited as research assistants. Training will be conducted where they will be informed about the research aims, objectives and the significance of the study. They will be trained about the methods of data collection of the study. They will be taught about the ethical considerations as well as their role in the study. They will further be familiarized with the tools that will be used for data collection to ensure reliability and standardization among the data collectors. The training will be done using the guidelines for collecting data in studies of soccer developed by the FIFA (Fuller et al., 2006) and the UEFA (Hägglund, Waldén, Bahr, & Ekstrand, 2005). The training will be conducted in a youth team that will not participate in the main study. Discussions and consultations among the research team members will be organized to ensure common understanding and performance of the measurement and recordings. They will also be trained on the standardized way of communicating with coaches and medical personnel regarding questions that may be asked.

Coaches and assistant coaches of the teams in the first and second division will be approached by the researcher where they will be explained the aims, objectives, rationale and procedure for the study. Further appointments will be organized for more explanation and opportunity to ask any questions pertaining to the study. Verbal explanations will be provided to the coaches in addition to the participant information sheet requesting them to participate in the study. Henceforth written consent will be sought from the coaches signing the consent form. This will be done during the preseason period.

The coaches will be requested to allocate time that will be convenient for them and the players to perform the measurement and test pertaining to the study.

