### **2.3.9 Statistical analysis**

All data will be analyzed statistically using STATISTICA version 12. Standard descriptive statistics will be used for numerical variables as means, standard deviations (SD) or 95% confidence intervals (CI).

In this study incidence for all injuries will be expressed as injuries per 1000 soccer playing hours for the purpose of the comparison with previous epidemiological studies. Risk per 1000 hours of exposure either per match, training or both will be equal to number of injuries multiplied by 1000 per total exposure time. The variations of injuries during match, training or both for the two seasons will be analyzed using Analysis of Variance (ANOVA). ANOVA will also be used to analyze the occurrence of injuries according to the position in the team and division of play. The categorical variables such as the frequency, type, location, severity as well as the mechanism of injuries will be analyzed using a Chi-square test or Fisher's exact test for small numbers. Between groups incidence of injuries will be compared using z-statistics and rate ratios (RR) with a 95% CI will used to present data. The level of significance for all the tests is set to 0.05. Univariate and multivariate regression analyses will be used to calculate odds ratios (ORs) and 95% confidence intervals (CIs) for  $\pm 1$  standard deviation of change. The details of all the statistical analysis that will be performed are provided in the appendix J.

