#### **2.4.4 Participants**

Coaches and assistant coaches of the teams in the second division teams will participate in this study. The coaches have been the center of focus in recent years as the main actors in the development of soccer in Rwanda. Much training has been organized by FIFA and CAF to enhance the knowledge and practice of the coaches. Trainings pertaining to technical, tactical and physical performance of the players were provided. At the end of the training, coaches are provided certificates. Not all coaches in Rwanda are citizens and not all of them had the same training. There are therefore some differences that may arise from their coaching training, background and experience.

The coaches are required to plan and supervise training sessions to develop the fitness and the skills of the payers. Coaches are responsible for the development of the training sessions according to the demands of the competition and the period of the season. The involvement of the coach in the first division teams concerning injuries in Rwanda is relatively less compared to the coaches in the second division because the teams have medical personnel who provide assistance. They also have assistant coaches, sometimes goalkeeper coaches, and kit managers. Coaches in the second division do not have all the support needed for their work. Working with

young players, they are required to act as organizers, parents, teachers, counselors, discipliners, for them to achieve results. In the case of injuries, coaches are looked at as mature and responsible people to provide first aid, preliminary management and advice for treatment. Coaches are further responsible to allow the players to return to play after injuries.

There are 19 teams in the second division and each team has at least one head coach. The minimum number of coaches of the teams who will receive the training is 19. The assistant coaches and goalkeeper coaches of the teams in the intervention study will also participate in the study even though not all the teams have them. The total number of players participating in the in the second division league is 570.

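### Re-injury by medical support: one list of objectives drops the comparison, and no analysis in the available text separates support from division

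*Combined protocol and SAP*

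**What the plan says.** **Objective.** Section 1.3 (Study one, objective e) reads "To determine whether the availability of the medical support into the teams is associated with the incidence of re-injuries". Section 1.1 gives the motive: "there is a need to assess the incidence of the re-injuries among team that have and teams that do not have medical personnel". The methods chapter does not carry this through. The matching item in section 2.3.2 is "To describe the availability of the medical support into the teams", which has no outcome and no comparison.

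**Method.** Section 2.3.9 expresses incidence per 1000 hours, for matches, training or both, and then states: "Between groups incidence of injuries will be compared using z-statistics and rate ratios (RR) with a 95% CI will used to present data". No covariates are named, and nothing is said about players being grouped in teams. Division appears in an ANOVA of injury occurrence, but not as a covariate for this question. The section also says "Univariate and multivariate regression analyses will be used to calculate odds ratios (ORs) and 95% confidence intervals (CIs) for" changes of one standard deviation. That sentence names neither outcome nor covariates and does not mention re-injury or medical support. Further detail is deferred to Appendix J, which is not in the text available for review.

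**Who has staff.** Section 2.4.4 says first-division coaches are less involved with injuries than "the coaches in the second division because the teams have medical personnel who provide assistance". The teams with personnel in that sentence are the first-division ones. The section adds that second-division coaches lack full support and decide themselves when an injured player resumes. It does not say how many second-division teams have staff. Availability is to be collected by coach questionnaire (sections 2.4.5.1 and 2.4.7.1), and section 2.4.7.1 anticipates that new medical personnel may arrive between seasons.

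**The concern.** On the protocol's own description, the 14 first-division teams all fall in the supported group, and teams without staff are second-division teams. A crude rate ratio of supported to unsupported teams therefore carries any difference between divisions that affects re-injury for other reasons.

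Some such differences are documented. Section 2.3.4 gives the first division 26 matches from September to June, and the second division 11 to 12 matches from November to May. Per month that is 26/10 = 2.6 against 11/7 to 12/7 = 1.6 to 1.7. A rate pooled over match and training hours would reflect this different mix.

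At stake is whether the objective e result can be read at all. A benefit of support could be hidden or exaggerated, or a pure division difference could be taken for one. Support is also a property of the team, so a z-test that treats injuries as independent would give an interval that is too narrow.

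**Working it through.** The documents give no expected re-injury rate, event count or power for this comparison, so there is no planned figure to reproduce. The check is a sensitivity calculation.

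**Inputs from the documents**
- 14 first-division and 19 second-division teams (section 2.3.4).
- First-division teams have medical personnel (section 2.4.4), taken here as all 14.

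**Assumptions (not in the documents)**
- k = number of second-division teams with staff, 0 to 10.
- R = first-to-second-division re-injury rate ratio for reasons other than support, 1.5 or 0.67.
- Equal exposure per team.

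**Step 1. Crude ratio when support has no effect.** The supported group is 14 teams at relative rate R and k teams at rate 1. The unsupported group is 19 − k teams at rate 1. So

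crude ratio = (14R + k)/(14 + k).

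| k | First-division share of supported teams | R = 1.5 | R = 0.67 |
|---|---|---|---|
| 0 | 14/14 = 100% | 21/14 = 1.50 | 9.38/14 = 0.67 |
| 5 | 14/19 = 74% | 26/19 = 1.37 | 14.38/19 = 0.76 |
| 10 | 14/24 = 58% | 31/24 = 1.29 | 19.38/24 = 0.81 |

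The true ratio is 1 in every cell.

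**Step 2. With a real effect.** If support multiplies the rate by the same factor in both divisions, the crude ratio is that factor times the table entry. For an assumed true ratio of 0.75, R = 1.5 gives 0.75 × 1.29 = 0.97 (k = 10) to 0.75 × 1.50 = 1.13 (k = 0). R = 0.67 gives 0.75 × 0.67 = 0.50 (k = 0) to 0.75 × 0.81 = 0.61 (k = 10). The same benefit is hidden or reversed in one case and exaggerated in the other.

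**Step 3. Weighting by season length.** With exposure proportional to 10 and 7 months, the ratio is (140R + 7k)/(140 + 7k). At k = 10 this is 280/210 = 1.33 for R = 1.5 and 163.8/210 = 0.78 for R = 0.67. Equal exposure is therefore not the assumption that creates the bias; this weighting makes it slightly larger.

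**Step 4. What adjustment can recover.** With all 14 first-division teams staffed, everything known about support after adjusting for division comes from within the second division. The team-level correlation phi between support and division, and the approximate variance inflation 1/(1 − phi²), are:

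| k | Staffed v. unstaffed, second division | phi | Variance inflation |
|---|---|---|---|
| 0 | 0 v. 19 | 1.00 | not estimable |
| 2 | 2 v. 17 | 0.88 | 4.6 |
| 5 | 5 v. 14 | 0.74 | 2.2 |
| 10 | 10 v. 9 | 0.53 | 1.4 |

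**The case against.** **No test is assigned to objective e.** This stands. A reader might infer that the comparison is definitely planned unadjusted. The documents do not show that: regression is listed, Appendix J could not be checked, and section 2.3.2 does not carry the comparison forward. What can be said is that the available text specifies no adjusted analysis for it. The regression sentence does not fill the gap. Odds ratios per standard deviation suit continuous player measurements, not a yes/no attribute of a team.

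**Rates per 1000 hours already handle season length and match load.** Partly true. Season length enters the denominator, and match-specific rates would remove the difference in mix. But section 2.3.9 leaves open which rate is used here, and other division differences remain.

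**The objective claims only an association.** True, but an association that may be nothing more than division does not answer the question raised in section 1.1.

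**The size is assumed.** This stands. Neither k nor R is in the documents, and R could lie closer to 1. A reader might infer that the bias specifically masks a protective effect because the first division plays more. The documents do not fix even its direction.

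**Physiotherapists in unstaffed teams.** Study assistants are physiotherapists (section 2.3.6.1) and record injuries where a team has no medical staff (section 2.3.5.4). A reader might infer that no truly unsupported group exists. The documents describe these assistants only as data collectors and give them no treatment or clearance role. Informal care is possible but undocumented, and should not be stated as fact.

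**Conclusion.** The point holds in limited form. Sections 1.3 and 2.3.2 disagree on whether re-injury is compared by medical support at all. If it is, the only between-group incidence method in the available text would confound support with division and ignore team clustering.

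With no true effect, the crude ratio would be 1.29 to 1.50 under a division rate ratio of 1.5, and 0.67 to 0.81 under 0.67. This rests on all first-division teams being staffed, 0 to 10 staffed second-division teams, equal exposure per team and the two illustrative division ratios. The bias is material across that range, but its true size and sign are unknown. That the comparison is simply one of divisions follows only if k is 0, which the documents do not say.

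This concerns a stated cohort objective, not the randomised comparison.

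**What to change.** 1. Reconcile sections 1.3 and 2.3.2: either keep the association or reduce it to a description in both.
2. If it is kept, specify in section 2.3.9 a re-injury rate ratio stratified by or adjusted for division, with an exposure offset, match and training hours separated, and errors clustered by team (with a small-sample correction, given the few teams).
3. Restrict it to season one, or adjust for randomised arm in season two. Sections 2.4.6 and 2.4.7.1 give intervention-group coaches in the second division warm-up and first aid training before season two, and section 2.2 mentions first aid, treatment and rehabilitation training for control-group coaches. Those accounts also need reconciling. Season one is the cleaner choice, because an arm term cannot remove training given to both arms.
4. State in advance that if no second-division team has medical staff, the result is reported as a division difference only. Label it exploratory in any case.
5. Optionally, add a line to the assistants' form for any care or advice given, so that the secondary question can be checked rather than assumed.

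The cost is wording plus, at most, one form line; division, team and exposure are already collected. The downside is a wide interval, since the contrast rests on at most 19 second-division teams and vanishes if none is staffed.
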